
##### Neuropsychological Tests

Parkinson’s disease has been associated with cognitive impairment across a range of domains, including aspects of cognitive flexibility, inhibitory control, sustained attention, and working memory (Owen et al., 1993; Uekermann et al., 2003; Kudlicka et al., 2011; Weintraub et al., 2018). The Cambridge Neuropsychological Test Automated Battery (CANTAB) for PD will be used for assessment of cognitive function. These will include; (a) Paired Associates Learning, (b) Pattern Recognition Memory, (c) One Touch Stockings of Cambridge, (d) Spatial Working Memory, and (e) Match to Sample Visual Search. Health-related quality of life will be assessed with the PD Questionnaire (Damiano et al., 1999). This neuropsychological data will be collected prior to participation commencement, at the end of the 10-week intervention, and at a 6-month follow-up, in the same session as the other behavioral assessments.

Fall rate will be recorded for a period of 1-year after completion of the exercise program. Falls rates will be considered a secondary outcome, due to concerns about the reliability and validity of self-report falls diary data. A fall will be defined as an unexpected event in which the participant comes to rest on the ground, or the floor (Mirelman et al., 2016). Several options will be used for the recording of fall events and to maximize the accuracy of reporting. Participants will receive fall calendars, either a paper version, a web-based calendar, or a smartphone application. Information logged in the online or smartphone-based calendars will automatically be uploaded to a database. Participants will be provided pre-addressed envelopes, and will be instructed to mail the paper version once every month. If a fall is recorded, the participant will be contacted by their treating therapist and asked when and how the fall occurred and whether there was any injury or need for medical treatment.

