## Methods

### Objectives

The aim of the proposed study is twofold. Behavioral analysis of gait and cognitive function together with PET and MRI brain imaging methods will be used to evaluate the molecular basis and neural underpinnings of (1) the decline of mobility function in PD, and (2) the effects of an engaging, cognitive game-based DT-walking program on mobility functions.

The first objective is to determine if the metabolic brain activity during single and DT treadmill walking is different in PD as compared to able-bodied age-matched controls. It is hypothesized that there will be significant changes in brain metabolic activity of several cortical and subcortical regions of the PD patients relative to able-bodied controls. This will be the case for both single and DT-walking conditions.

The second objective is to conduct a multi-centered, single-blind, randomized, two-arm, and parallel group-controlled trial and examine the effects of a 10-week DT treadmill training program: on (a) gate and cognitive function tested under single and DT conditions, (b) the pattern of metabolic brain activity quantified with single and DT-walking uptake periods, and (c) structural and functional changes (at rest) occurring prior to and after DT-walking training.

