**FIGURE 1 F1:**
[figure not shown]
Experimental timeline. Assessment days (ADay) indicate order of assessments. PET scans on ADay_3_ and ADay_4_ will be counterbalanced between a single-task treadmill walking only task and a DT treadmill walking and cognitive game condition. A final DT PET scan will be acquired following intervention (ADay_7_). MRI scans will be collected pre- (ADay_2_) and post-intervention (ADay_6_). Behavioral testing (Behav; including motor measures and neuropsychological testing) will occur on three occasions: prior to intervention (ADay_1_), following intervention (ADay_5_), and again after a 6-month follow-up. Fall-history and physical activity tracking will be acquired throughout, until 12-months post-intervention. Measures of gait will be acquired throughout the program, including during behavioral assessment days, at each training session, and on PET assessment days. The experimental (XG) and control arm (CG) groups will complete the entire timeline, while healthy controls (HC) will complete up until ADay_4_.

Participants in the CG group will complete 10 weeks of a “single-task” exercise program including videogames only (i.e., for 10 min while sitting) and walking-only on the treadmill—these tasks are conducted independently, one at a time. Participants in the XG will perform various cognitive computer games during the warm up period on the compliant surface and during all treadmill walking intervals. The computer games will be played using the head mounted IB-mouse as described above. Many inexpensive and easily accessible common and modern games exist which are visually rich, fun, and engaging. They include a variety of tasks that require; (i) visual search and tracking of multiple targets, (ii) speed accuracy requirements, (iii) presence of distracters, (iv) matching tasks, and (v) working memory. Note that the games that will be used during behavioral and PET assessments and those used in the XG exercise program are different.

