##### Physical Activity Tracking

In the second week of the exercise, program participants will be given a Fitbit watch (Ionic) to track physical activity levels during waking hours (Liang et al., 2018; Tedesco et al., 2019; Fuller et al., 2020). This model records steps taken, GPS and heart rate. Participants will be shown how to use the watch and how to access and transfer the stored data. Recorded activity data from the watch will be transferred to the therapist once a week during a treatment session. Over a 10-week time period this will provide ample practice on how to use the Fitbit watch and how to access and transfer its recorded activity data. Following the 10-week exercise program, the participants will be shown how to transfer their activity data to the research team. They will be instructed to do this once a week. Participants will be sent an e-mail or text message to remind them to do so.

Walks of more than 1 min will be determined by data showing continuous steps and where there are concurrent and adequate changes in GPS and increased heart rate. For each walking bout exceeding 1 min, the walking distance will be determined using the GPS data. The main physical activity outcome measures will be the total monthly walking duration and walking distance. Walking speed will also be computed for each walking bout over 1 min, and a monthly average obtained. Following the exercise program, all participants will be contacted by phone once a month to remind them of the use of the physical activity tracker.

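### Fall details are collected only after a participant logs a fall, and by the treating therapist who knows the arm; a forgotten calendar month could be mistaken for a fall-free one

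*Protocol article*

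**What the plan says.** The Neuropsychological Tests section of the protocol article sets out how falls are collected. "Fall rate will be recorded for a period of 1-year after completion of the exercise program". Participants use a paper, web or smartphone calendar. Paper calendars are mailed in monthly, and electronic entries upload by themselves. The one follow-up step described is: "If a fall is recorded, the participant will be contacted by their treating therapist and asked when and how the fall occurred". The same call also covers injury and medical treatment. The section ranks the outcome with a caveat: "Falls rates will be considered a secondary outcome, due to concerns about the reliability and validity of self-report falls diary data".

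Three other places bear on this:

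- Objectives describes a "multi-centered, single-blind, randomized, two-arm, and parallel group-controlled trial" and does not name the blinded party.
- Intervention Protocol (text after Figure 1) shows how the arms differ: "Participants in the XG will perform various cognitive computer games during the warm up period on the compliant surface and during all treadmill walking intervals". Control participants play seated and then only walk. Physical Activity Tracking places the therapist at these sessions: "Recorded activity data from the watch will be transferred to the therapist once a week during a treatment session".
- Physical Activity Tracking also plans, after the program, that "all participants will be contacted by phone once a month to remind them of the use of the physical activity tracker". No falls question is attached to that call.

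**The concern.** Two features of the collection method deserve attention.

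First, the contact depends on the participant having logged a fall. Someone who forgets the calendar for a month triggers no contact, and the article describes no reminder or chase for a missing calendar. For the web and app versions only logged information is uploaded, so as described an empty month may mean either no falls or no reporting.

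Second, the person who asks about a logged fall delivered the training and knows the arm. Knowledge of the arm can affect how questions are put and how answers are written down.

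Fall rate is compared between XG and CG in the mixed-model ANOVA, with 6- and 12-month times (Statistical Analyses). Falls that nobody asked about cannot be recovered at the analysis stage, so the time to settle this is before follow-up starts.

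**Working it through.** The article gives no fall rate, no calendar return rate and no power calculation for falls, so there is no figure of the plan to reproduce. The check has a reading of the text and an illustration.

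**Reading the sections together**

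1. Trigger: a logged fall (Neuropsychological Tests). No falls contact is described when nothing is logged.
2. Caller: the treating therapist (same section).
3. Is the caller aware of the arm? The arms differ visibly in every session, and the therapist is present at sessions (Intervention Protocol; Physical Activity Tracking). So yes.
4. Existing contact with everyone: a monthly phone call after the program, with the activity tracker as its only stated purpose (Physical Activity Tracking).

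**Illustration: what blank months could do**

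Let the true monthly fall rate be λ in each arm, M the months of follow-up, and r the share of months returned. Assume that falls are unrelated to return.

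- If blanks count as zero, the observed rate is λ·M·r / M = λ·r. Hence observed rate ratio = true rate ratio × r(XG) / r(CG).
- If falls are divided by returned months, the observed rate is λ·M·r / (M·r) = λ. The ratio is then unaffected by return.

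The return shares below are assumptions. The true ratio is 1.0 and blanks count as zero.

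| Return XG | Return CG | Apparent XG/CG ratio |
|---|---|---|
| 90% | 90% | 0.90/0.90 = 1.00 |
| 75% | 90% | 0.75/0.90 = 0.83 |
| 90% | 75% | 0.90/0.75 = 1.20 |
| 80% | 90% | 0.80/0.90 = 0.89 |
| 90% | 80% | 0.90/0.80 = 1.13 |

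Equal return leaves the ratio alone and only understates both rates. Unequal return moves it in favour of whichever arm returns less.

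**Illustration: what the call could do**

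This applies only if the call could remove an event from the count, which the article does not say. If 10% or 20% of XG falls were struck out and none in CG, a true ratio of 1.0 would appear as 0.90 or 0.80.

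**The case against.** The case against is substantial, and most of it stands.

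- A reader might infer that unreturned calendars are counted as no falls. The article sets no such rule. The handling of missing months, and the denominator, are commonly left to the full protocol or the analysis plan, neither of which is shown. This stands: the text supports only that the two could be confused.
- A reader might infer that the therapist adjudicates falls. The call asks about time, circumstances, injury and treatment, after the participant has already logged the event. Nothing says that it confirms or deletes a fall. This also stands: the direct exposure is of fall detail, and of the count only if events are reclassified.
- A reader might see a contradiction with the single-blind label. The blinded party is not named, and a therapist cannot be blinded to the training given. There is no contradiction.
- A reader might assume that the bias would flatter the experimental arm. The program is presented as engaging, so XG might as easily return more calendars, which would work against it. Nothing in the article ties reporting mode to arm either.
- The Figure 1 legend says that fall history is gathered through to 12 months after the intervention, and there is a 6-month behavioral visit. The article does not say that falls are asked about at that visit, but it would be too strong to claim that no other falls contact exists.
- The authors have already ranked falls as secondary because they doubt diary data, and they offer three recording modes to improve reporting.

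What the objection does not remove is the stated method itself. The trigger and the caller are explicit choices about data collection, not details left for later. An analysis plan cannot supply falls that were never asked about.

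**Conclusion.** The point holds in a limited form and is minor. As described, fall details are gathered only after a logged fall and by someone who knows the arm, and a forgotten month could be mistaken for a month without falls. Whether this biases the XG-CG comparison cannot be determined from the article. Bias from blank months would need blanks to be treated as zero and return to differ between arms. With assumed returns of 90% and 75% the apparent ratio would be 0.83 or 1.20, depending on which arm returns less, and with equal return it would be 1.0. Bias in the count from the therapist's call would need a reclassification step that is not described. The outcome is secondary and its weakness is acknowledged, so this is an inexpensive improvement to data collection and not an error that threatens the trial's main conclusions.

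**What to change.** 1. Add a scripted question on falls in the past month to the monthly phone call already planned for all participants, asked in both arms whether or not a fall was logged.
2. Have that question, and any query on a logged fall, put by existing study staff who do not deliver treatment and who are, where possible, unaware of arm.
3. Count a month as observed only if there is a calendar or a call response for it, and compute falls per observed month. This removes the effect of unequal return so long as falls are unrelated to return.
4. State whether the query on a logged fall can change the count.

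The cost is a slightly longer call and some reassignment among existing staff. Callers must ask participants not to reveal their program. Participants still know their own training, so bias from unblinded self-report remains.

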##### Physical Activity Tracking

In the second week of the exercise, program participants will be given a Fitbit watch (Ionic) to track physical activity levels during waking hours (Liang et al., 2018; Tedesco et al., 2019; Fuller et al., 2020). This model records steps taken, GPS and heart rate. Participants will be shown how to use the watch and how to access and transfer the stored data. Recorded activity data from the watch will be transferred to the therapist once a week during a treatment session. Over a 10-week time period this will provide ample practice on how to use the Fitbit watch and how to access and transfer its recorded activity data. Following the 10-week exercise program, the participants will be shown how to transfer their activity data to the research team. They will be instructed to do this once a week. Participants will be sent an e-mail or text message to remind them to do so.

Walks of more than 1 min will be determined by data showing continuous steps and where there are concurrent and adequate changes in GPS and increased heart rate. For each walking bout exceeding 1 min, the walking distance will be determined using the GPS data. The main physical activity outcome measures will be the total monthly walking duration and walking distance. Walking speed will also be computed for each walking bout over 1 min, and a monthly average obtained. Following the exercise program, all participants will be contacted by phone once a month to remind them of the use of the physical activity tracker.

#### Image Acquisition

##### PET Data

All subjects will undergo two pre-intervention [^18^F] FDG-PET scans after fasting for at least 6 h before scanning. A head CT scan will be acquired for attenuation correction purposes. Static images (10 min) will be acquired starting 40 min after injection. During the FDG uptake period, participants will perform in different sessions, on different assessment days; (a) treadmill walking only (test session 1) and (b) DT treadmill walking (test session 2; see Figure 1). The order of the walk-only and DT-walking sessions will be counterbalanced. The single and DT treadmill walking will be done for 28 min each. This will involve seven 3-min walk intervals with 1-min rest periods (standing). Walking speed and duration will be carefully controlled, and repeated for each test session (i.e., single and DT conditions, pre- and post- intervention). Seven different standardized cognitive games will be selected for the seven DT-walking intervals. These will include; (a) five 3-min VC games with different difficulty levels (i.e., increasing game speed, adding distractors, and changing path of target motions), and (b) two 3-min VMT games, one played using horizontal head rotations and one with vertical head rotations. The PD patients will repeat the DT-walking PET imaging protocol after completion of the 10-week exercise program.

##### MRI Data

All participants will undergo an MRI session before the intervention, Data collected will include a structural, T_1_-weighted anatomical image, a T_2_^∗^-weighted resting state fMRI scan, pCASL, and DTI data. Following the intervention, all PD participants will undergo a second MRI session, including the same scans as those acquired before intervention.

First, structural T_1_-weighted (T1w) MR images will be acquired, using a 12-channel head and neck coil. T1w data will be acquired using an MP-RAGE sequence with TR/TE/TI = 2300/3.02/900 ms, 240 slices, flip angle = 9, FOV = 256 mm × 256 mm, 1.0 mm^3^ (isotropic) resolution. This T1w data will provide the anatomical data over which the PET, RS-fMRI, pCASL, and DTI will be overlaid. Although MRI data cannot be used to directly investigate neural changes occurring during DT-walking, this technology will provide valuable information regarding how brain function and structure may change before and after DT-training in PD participants.

RS-fMRI data (T_2_^∗^-weighted) will be collected using a gradient-echo, echo planar imaging (GE-EPI) sequence with the following parameters: TR/TE = 2000/28 ms, 240 slices, flip angle = 77, FOV = 220 mm × 220 mm^2^, 3.4 mm × 3.4 mm × 4.0 mm resolution. The parameters for the resting state pCASL data are as follows: TR/TE = 4000/12, 20 slices, flip angle = 90, FOV = 240 mm × 240 mm^2^, 3.8 mm × 3.8 mm × 5.0 mm resolution, inter-slice space = 1 mm, labeling time = 2.0 s, post label delay time = 1.2 s, bandwidth = 3 kHZ/pixel. For each participant, 45 label/control image pairs will be acquired. DTI data will be acquired using a single-shot spin echo, echo planar imaging sequence with the following parameters: 35 directions (*b* = 700 s/mm^2^), TR/TE = 10413/70.8 ms, FOV = 240 mm × 240 mm × 163 mm, 65 transverse slices, 2.5 mm^3^ (isotropic) resolution.

### Data Analysis

Details of the analysis procedures used to quantify the following spatio-temporal gait variables, and the VMT and VCG performance measures have been published elsewhere (Nankar et al., 2017; Szturm et al., 2017; Ahmadi et al., 2019). In brief, the following spatio-temporal gait variables were computed from the center-of-pressure of foot displacement time series recordings; (a) step length (SL), the distance between two successive heel contacts in the AP direction, and (b) swing time (SW) time, the time between toe-off and heel contact of each leg. The average SL and SW were then determined for each 1-min walk trial. Variability measures quantify the inter-stride fluctuations in SL and SW around the mean value and will be report it as coefficient of variance, COV-SL and COV-SW. The location of all heel contacts during each 1-min walk trial were also determined in both AP and ML directions. The dispersion of heel contact locations will be computed as the COV, and reported as AP-drift and ML-drift.

Figure 2 illustrates the VMT and VCG game tasks and plots of game movement responses. The following outcome measures for the VMT task include: (a) total residual error (TRE), determined by computing the difference between the trajectories of the target and head cursor motions, (b) amplitude variability (AV), a measure of movement consistency determined as the coefficient of variation of the mean right-to-left and left-to-right tracking movements for 20 cycles (i.e., a 45 s. trial). The following performance measures for the VCG will be quantified: (a) success rate (SR), (b) response time (RT), and (c) movement variance (MV).

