##### Motor and Gait Assessment

Behavioral assessment of each PD participant will be conducted on three occasions, before and after a 10-week exercise program, and at a 6-month follow-up time period. Healthy control participants will be assessed at time 1 only. PD participants will initially be assessed with the Part-III (motor) section of the Movement Disorder Society—Unified Parkinson Disease Rating Scale [MDS-UPDRS (Goetz et al., 2008)]. Assessment of gait function under single-task (walk only) and DT conditions will be conducted on a treadmill, instrumented with a pressure mapping system. Treadmill walking is used to obtain 40–60 consecutive steps and at a constant speed [see Bhatt (2018) and Szturm et al. (2017) for a detailed description of data recording, analysis, and test-retest reliability]. Participants will be instructed to walk on the treadmill at their preferred gait speed without hand support for four 1-min intervals (one single-task walking only, one VMT, and two VCG trials, described below). The center-of-pressure of foot displacement in the mediolateral (ML) and anteroposterior (AP) directions will be collected at 100 Hz.

A custom computer application with the following two assessment modules will be used for the DT test conditions: (a) a visuomotor tracking (VMT) task and (b) a visuospatial cognitive game (VCG) task. Figure 2 illustrates the gaming set-up for the VMT and VCG tasks. As described previously (Nankar et al., 2017; Szturm et al., 2017; Ahmadi et al., 2019; Mahana et al., 2021), an IB-mouse will be used to control and interact with the cognitive assessment games. The VMT task used in the present study requires real-time, on-line visual feedback of the relative positions of two objects. The VCG task requires visual search to locate target objects and cognitive inhibition to avoid distractors. The VMT and VCG tasks require precision head-pointing movement. Many real-life tasks involve head movements to track and locate various objects, and for information processing of what are being seen. The increased visuospatial processing necessary to maintain walking rhythm and to correct for any drifting on the treadmill would compete for resources required to perform the VMT and VCG tasks, and vice versa.

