#### Statistical Analyses

Our sample size was calculated based on our previous work involving PET imaging in PD in which participants were randomized into either gene therapy or sham-surgery groups, and assessed at 6 months follow-up (Ko et al., 2014a). With anticipated ρ2 = 0.673 [20% more than what is expected for placebo effect-related pattern’s explanation of clinical benefits induced by sham surgery over 6-months (Ko et al., 2014a)], G^∗^Power (version 3.1.9.2; RRID:SCR_013726) estimates the minimal sample size to be 12 (effect size f2 = 2.060). With maximally anticipated drop-out rate of 10% (e.g., motion artifacts, patient’s voluntary withdrawal, etc.); we require 13 subjects per group/site.

MATLAB (The Math Works Inc., Natick, MA, United States version 2010a) will be used to compute the outcome measures. Normality of the data will be assessed using the Shapiro-Wilks test. Sphericity will be assessed using Mauchly’s test. For normally distributed data sets, a mixed-model ANOVA will be used to examine the effects of time (pre– and post-intervention), group (XG and CG) and interaction of time^∗^group of all behavioral outcome measures (gait, cognitive, neuropsychological, fall rates, physical activity levels, and health-related quality of life). Note the time factor for fall rates, physical activity outcome measures, and health-related quality of life will include the 6-month and 12-month follow-up time periods. Non-normally distributed data will be assessed using the Wilcoxon-Signed rank test to determine differences between pre- and post-intervention. The significance level will be set at *p* < 0.05, and statistical analysis will be conducted using SPSS (v.22; SPSS Science, Chicago, IL, United States).

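### AP-drift and ML-drift are coefficients of variation of a belt coordinate, so they mix mean position and choice of origin with dispersion; the SD in length units would not

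*Protocol article*

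**What the plan says.** The Data Analysis section of the protocol article derives the treadmill gait variables from foot centre-of-pressure recordings. Step length is defined as a distance between contacts: "step length (SL), the distance between two successive heel contacts in the AP direction". Swing time is a duration. The variability of both "will be report it as coefficient of variance, COV-SL and COV-SW".

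The section then turns to position: "The location of all heel contacts during each 1-min walk trial were also determined in both AP and ML directions". The next sentence fixes the statistic for these positions: "The dispersion of heel contact locations will be computed as the COV, and reported as AP-drift and ML-drift".

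The signal itself is described under Motor and Gait Assessment: "The center-of-pressure of foot displacement in the mediolateral (ML) and anteroposterior (AP) directions will be collected at 100 Hz". Neither section states a coordinate origin, a reference point or any centring. The Data Analysis section opens by deferring detail: "Details of the analysis procedures used to quantify the following spatio-temporal gait variables, and the VMT and VCG performance measures have been published elsewhere".

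Under Statistical Analyses, the mixed-model ANOVA tests time, group and the "interaction of time^∗^group of all behavioral outcome measures (gait, cognitive, neuropsychological, fall rates, physical activity levels, and health-related quality of life"). Both drift variables therefore enter the comparison of the two training arms. The same part of the article also plans correlations of neural change with gait measures.

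**The concern.** The article carries one statistic over from intervals to coordinates. For an interval such as step length, zero means no length, so the SD as a fraction of the mean is a sensible relative spread. For a location, zero is a feature of the measuring equipment. The denominator is then the average distance of the feet from that zero, which has no bearing on how steadily the participant walks.

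A participant who settles further forward or further back on the belt after training would show a changed AP-drift with an identical scatter of foot placements. A real reduction in scatter could equally be cancelled by a shift in position. Even without a systematic shift, differences between people in where they walk are added to the measure as noise. If the map origin differs between the two sites, which the article does not say, the COV takes up that difference and the SD does not.

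Constant treadmill speed does not settle the matter, because it does not fix position on the belt. The Motor and Gait Assessment section itself expects participants to be correcting for drift while the cognitive task competes for the same resources.

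**Working it through.** The article reports no value for AP-drift or ML-drift, so there is no figure to reproduce. The check is algebra, illustrated with assumed values.

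**From the article:** the variable is heel-contact location (AP and ML, per 1-min trial), and the statistic is the COV. **Assumed, because the article gives none:** every SD and mean position below.

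**Step 1: effect of the origin or mean position.** COV = SD / mean. If the origin or the average walking position moves by c, the SD does not change, but COV = SD / (mean + c). Step length is a difference between two locations, so c cancels and its COV is unaffected.

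**Step 2: same dispersion, different position.** With SD = 25 mm:
- mean 200 mm: 25/200 = 12.5%
- mean 250 mm: 25/250 = 10%
- relative change: (10 − 12.5)/12.5 = −20%, with the scatter unchanged

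Over a wider AP range with SD = 5 cm:

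| Mean position (cm) | COV | SD (cm) |
|---|---|---|
| 20 | 25.0% | 5 |
| 40 | 12.5% | 5 |
| 60 | 8.3% | 5 |
| 80 | 6.25% | 5 |
| 100 | 5.0% | 5 |

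**Step 3: a real change hidden or reversed.** Start at SD 4 cm and mean 40 cm: COV = 10%. Let the SD fall by 25% to 3 cm.
- mean stays at 40 cm: 3/40 = 7.5%, so the COV follows the SD exactly
- mean moves to 30 cm: 3/30 = 10%, so the improvement disappears
- mean moves to 20 cm: 3/20 = 15%, so the improvement appears as a worsening

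**Step 4: the ML direction.** With SD = 3 cm, the COV is 8.6% at a mean of 35 cm, 12% at 25 cm, 20% at 15 cm and 60% at 5 cm. It is 600% at 0.5 cm and −30% at −10 cm. The last two values arise only if the origin lies near the walking line or on the other side of it. With an origin at a side edge of the mat the ratio stays positive and stable.

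**Step 5: one point about the replacement.** If left and right contacts are pooled in the ML direction in equal numbers, and the two feet have the same within-foot variance and mean positions w apart, the pooled variance is approximately the within-foot variance plus w²/4. A pooled ML SD would therefore count step width as drift. Computing it per foot removes that term.

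**The case against.** The strongest reply is that the article only summarises its methods and refers the detail to earlier publications, where the origin and any referencing may be given. That would excuse an omission. Here, however, the sentence states the statistic positively. If the earlier papers used a referenced or origin-free measure, the sentence misdescribes it; if they used the raw COV, the flaw is present. The sentence needs correcting either way.

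A second reply is that position may hardly vary. Treadmill speed is constant, a harness attached to a support structure is worn at gait assessments, and the monitor stands at the front of the treadmill. With a fixed origin at a mat edge and a stable mean position, the distortion would be small. This stands: these features make a shift less likely, though they do not exclude one. It is also true that biasing the time-by-group interaction requires position to shift differently in the two arms, and nothing in the article shows that it would.

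A reader might infer more than the article supports:
- **That drift ceases to measure dispersion.** It does not: at a fixed mean the COV is proportional to the SD (Step 3, first line).
- **That ML-drift will explode or change sign.** This depends on an origin near the walking line, which the article does not state.
- **That a comparison of patients with healthy controls on drift is compromised.** No such test is stated. The behavioural ANOVA compares the two training arms, and the stated patient-control comparison concerns PET metabolic activity.

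**Conclusion.** The point holds in a limited form. As defined, AP-drift and ML-drift depend on the coordinate origin and on mean belt position in addition to dispersion, and a change in position can create or mask a change in drift. That follows from the definition alone.

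The size of the effect cannot be established from the article. The 20% artefact and the five-fold AP range above rest entirely on assumed SDs and positions, and the true distortion could be negligible.

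The reach is narrow. These are two of the six treadmill spatio-temporal variables (the others are mean step length, mean swing time and their COVs), alongside the 6-min walk test and overground speed. They are not named as primary. The effect is confined to them, their time-by-group tests and any correlation with imaging change that uses them. The correction is worth making because it is nearly free and removes the ambiguity completely.

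**What to change.** Replace the sentence in the Data Analysis section with a definition of AP-drift and ML-drift as the SD, in mm, of heel-contact location within each 1-min trial, computed separately for each foot in the ML direction.

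If a scaled version is wanted, divide by a quantity that training cannot change, such as body height. Mean step length is unsuitable: it is itself an outcome, and it is among the variables that the feasibility study under Anticipated and Preliminary Results reports as improved after training. Dividing by it would lower drift whenever steps lengthen, even with the same scatter.

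Keep the COV for step length and swing time. The COV of location can be tabulated as a supplement if comparability with earlier work matters, with the coordinate origin stated.

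The cost is one sentence and a small change to the code on the same recordings. No extra data or participants are needed. The only loss is direct comparability with any earlier paper that used the COV of location, and the supplementary table covers that.
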